### Study design

The MOMI Consortium progressed through three phases. The pre-pilot phase focused on sample quality assessment. The pilot phase was dedicated to the development and validation of the analytical workflows, while simultaneously harmonising the MOMI dataset, study outcomes, and analytical approaches [16,17,19,23,24]. The current phase (**Figure 3**) implemented population-scale molecular profiling of relevant specimens and continues with ongoing site-specific and cohort-wide data analysis and integration. Analyses are being performed on specimens collected during early (enrolment at <20 or <24 weeks GA), mid (22–28 weeks GA), and late pregnancy (28–36 weeks GA). These time points were selected to determine the dynamic trajectory of analytical factors throughout pregnancy, and test whether specific molecular signatures at one or multiple time points can predict the risk for specific APOs. Clinically, the earlier a risk for a specific APO can be identified, the higher the potential for adequate surveillance, improved clinical care, and prevention or reduced severity of the APO. Among the omics-platforms applied, metabolomics and proteomics will be applied to all longitudinal maternal specimens and cord blood, while the genomics analysis requires only a single sample from mother and infant. Maternal GARBH-INi specimens will also undergo genomics analysis. A sub-cohort study will include the longitudinal specimens of women with the most common APOs (PTB and SGA) and rare APOs (SB, very PTB, PE) plus a random sample from the full cohort (n = 5000) and 1000 women from the GARBH-INi cohort. These specimens are being analysed for nutrients group I, while in the GARBH-INi cohort, they are also being investigated for common bioanalytes and for proteomic and metabolomic APO signatures identified in the MOMI cohort. A nested case-control study (1:3) of the sub-cohort will consist of all specimens from women with rare APOs compared to women with term birth to test for biomarkers of epigenomics, nutrients of group II, and common bioanalytes. The common bioanalytes were selected based on their association with specific APOs and will only be measured at time points relevant to their role in pregnancy. Specifically, thyroid-stimulating hormone and pregnancy-associated plasma protein A will be tested in early pregnancy, whereas soluble fms-like tyrosine kinase and placental growth factor will be tested at mid and late pregnancy [25-31]. Placental tissues from a subset of women with PTB or term birth will undergo histopathology, transcriptomic, epigenomic, and global proteomic analysis.

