## DATA HARMONISATION

The Consortium has developed a harmonised framework for sociodemographic, clinical, and phenotypic variables across the biorepository sites. Specifically, SAS/STATA programmes were developed for harmonising site-specific data sets and quality control programmes for ensuring data consistency, while all harmonised datasets will be uploaded to a centralised platform. The biorepository sites upload clinical and phenotypic metadata that can be accessed by the analytical partners, who, conversely, upload their respective analytical data for cohort investigators. Although the GARBH-INi data, in compliance with government regulations in India and the GARBH-INi funding structure, are controlled by their team, data and analyses pipelines have been harmonised with the overarching MOMI Consortium. A first critical step was the harmonisation of birth outcome data, first on a site-specific level and then through central adjudication for confirmation.

PTB was defined as babies born alive before 37 weeks of pregnancy are completed [32]. Three subcategories were defined based on the GA: extremely preterm (<28 weeks, 0 days GA), (very preterm (28 weeks, 0 days to 31 weeks, 6 days GA), and moderate to late preterm (32 weeks, 0 days to 36 weeks, 6 days GA). The GA assessment was based on the Hadlock formula, which was implementable across all sites; missing head circumference data at AMANHI sites prevented the implementation of INTERGROWTH-21st formula. At time points with available ultrasound data, the GA was computed using either crown rump length or a composite of femur length and biparietal diameter. For the purpose of this study, preterm stillbirths will be evaluated as a part of SB outcomes.

SGA was defined based on the INTERGROWTH-21st standards [33] using the 10th percentile as cut-off. Only some cohort sites were able to define fifth or third percentile SGA babies. Due to discrepancies in the measurement of birth weight among the different cohort sites, birthweights were coded as level 1 or 2 when birthweights were measured within 48 or 72 hours of delivery, respectively, and as level 3 when measured at three days or later.

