SB was defined as delivery of a foetus at or after 22 weeks of gestation with no signs of life upon delivery. Among total SB cases, we classified early SB as birth prior to or at 22 weeks, 0 days to 27 weeks, 6 days of GA, and late SB when it occurred at 28 weeks, 0 days GA or later. Otherwise, SB of PTB babies were included in SB case numbers. Clinical data were used to adjudicate antepartum SB (Figure S2 in the **Online Supplementary Document**). Antepartum SB was considered priority 1 when cardiotocographic or ultrasound data of foetal death before onset of labour or rupture of membranes were available. Evidence of maceration, mummification, or other signs of putrefaction of the stillborn foetus was ascribed as priority 2 antepartum SB. An absence of perceived foetal movements as reported by the mother before the onset of labour or rupture of membranes was termed priority 3 antepartum SB.

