**SGA**							
SGA <10th percentile	434 (16.84)	936 (25.68)	1044 (34.80)	683 (27.32)	430 (9.55)	3527 (21.74)	2402 (29.65)
SGA <3rd percentile	167	385	525	304	170	1551	1167
**Stillbirth**	62 (2.41)	25 (0.69)	21 (0.70)	31 (1.24)	29 (0.64)	168 (1.04)	168 (2.07)
**Total number of APOs**	804 (31.21)	1380 (37.87)	1438 (47.94)	1125 (45.00)	825 (18.33)	5572 (34.35)	3500 (43.20)

AMANHI – Alliance for Maternal and Newborn Health Improvement, APO – adverse pregnancy outcome, GAPPS – Global Alliance to Prevent Prematurity and Stillbirth, MOMI – Multi-Omics for Mothers and Infants, PE – preeclampsia, PTB – preterm birth, SGA – small for gestational age

*Very PTB is defined as birth <31 weeks/6 days gestational age.

†Due to missing GA at birth, early-onset and late-onset PE cannot be derived for n = 2.

Thus, we have established a unique two-continent spanning cohort of pregnant women in LMICs, of which more than a third experienced APOs. Thousands of longitudinally collected specimens are now being analysed for genetic, proteomic, metabolomic, or nutrient factors associated with specific pregnancy outcomes. According to the study design (**Figure 3**), specimens from a single time point were selected for genomics analysis, whereas proteomic and metabolomic signatures will be determined using over 30 000 longitudinally collected maternal plasma samples (Table S1 in the **Online Supplementary Document**). Nutrients type I will be measured in >9500 maternal plasma and urine samples, and approximately 1200 maternal plasma samples for nutrients type II (Table S1 in the **Online Supplementary Document**). Specimen numbers for placental tissue analysis are listed in the relevant section below. To gain insights into potential biological factors that may impact infant morbidity and mortality and, considering the complex interactions of the mother-infant dyad, the same analytical tools are being applied to cord blood samples (Table S1 in the **Online Supplementary Document**).

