## DATA ANALYSIS AND DATA INTEGRATION

The analytical objectives of MOMI are to determine the omics signatures of each week of advancing GA (*i.e.* temporal pregnancy progression), the strength of association of each omics or other analytical platform with each APO through machine learning modelling (thereby identifying unique features of each APO phenotype), and how site-specific effects can be used to inform model generalisation. Analysis will proceed systematically from using risk signatures derived from a single platform to signatures identified through integration of multiple omics risk signatures, and from individual cohorts to cross-cohort integration. The integration of phenotypic metadata, including sociodemographics and clinical variables, will further enhance the understanding of biological mechanisms underlying APOs and improve prediction of APOs.

The structural heterogeneity across global cohorts presents a central analytical challenge that will be addressed by explicit methodological safeguards against batch effects, missingness, site heterogeneity, and overfitting. The MOMI analytical framework is built on a mature and extensively validated computational pipeline developed and applied across multiple large, multi-site pregnancy cohorts, including prior MOMI studies [17,19] and in subsequent multi-omic integration and machine-learning frameworks [15,18,20,21]. In these works, we have implemented harmonised preprocessing and quality control, explicit modelling of batch and site effects, and integration strategies that preserve biological signal while mitigating technical variation (*e.g.* empirical Bayes and factor-based normalisation, network-based integration, and multi-view latent variable models). Missing data are handled through a combination of modality-aware imputation and model architectures that accommodate partially observed samples, enabling inclusion of participants with incomplete data without introducing bias.

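### The assurance that women with incomplete data can be included free of bias cannot be supported for late-window or multi-time-point models, because very preterm birth itself removes the late specimen

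*Protocol article*

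**What the plan says.** The section on data analysis and data integration of the protocol article states: "Missing data are handled through a combination of modality-aware imputation and model architectures that accommodate partially observed samples". It adds that this has the effect of "enabling inclusion of participants with incomplete data without introducing bias". No missingness assumption is given. The text does not separate an assay that failed or was not run from a visit that could not take place because the pregnancy had ended.

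Other parts of the article bear on this:

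- **Windows.** The study design section sets the late window at 28–36 weeks. One purpose of the repeated sampling is to "test whether specific molecular signatures at one or multiple time points can predict the risk for specific APOs", so models that combine stages are planned.
- **Visits (Table 1).** After a visit at 26–28 weeks, GAPPS has visits at 32 and 36 weeks. After a visit at 24–28 weeks, AMANHI has one at 32–36 weeks. GARBH-INi has one at 30–32 weeks.
- **Outcomes.** The data harmonisation section ends the very preterm category at 31 weeks 6 days. The Table 2 footnote says "Very PTB is defined as birth <31 weeks/6 days gestational age". Either way, delivery is before 32 weeks 0 days. For stillbirth, "SB was defined as delivery of a foetus at or after 22 weeks of gestation".
- **Models.** Prediction uses gradient-boosted trees (XGBoost), with a separate model for each outcome and pregnancy stage, judged by AUROC and by the area under the precision-recall curve. The main safeguard is training on some sites and validating on held-out sites.

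**The concern.** Including incomplete participants is harmless only if absence of data carries no outcome information beyond what the model already conditions on. For late specimens the dependence is direct: a woman who delivers at 30 weeks has no 32-week specimen because she delivered at 30 weeks. That value does not exist, so it is not missing in the usual sense.

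If she stays in a late-window or multi-time-point model, there are two risks. A model that tolerates missing values may learn that absence of the late specimen means early delivery. An imputation that leaves a recognisable trace, such as a constant, lets a tree do the same. Apparent accuracy would then come from the calendar and not from biology.

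Held-out-site validation among the five GAPPS and AMANHI sites would not expose this, since their schedules share the feature. Bootstrapping stratified by site and outcome preserves it. Very preterm birth is a named rare outcome of the study, and its longitudinal samples are compared with those of term controls, so the affected models matter.

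**Working it through.** The challenged sentence carries no figure to reproduce. The check is of timing first, then of size.

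**1. Counts (Table 2).** Very preterm births at the five sites: 45 + 14 + 40 + 20 + 29 = 148, as the table states. This is 148/1587 = 9.3% of preterm births and 148/16 221 = 0.91% of pregnancies. GARBH-INi has a further 72.

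**2. Timing (Table 1 against the outcome definitions).**

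| Sites | First clearly late visit | Can a very preterm birth have that specimen, on schedule? |
|---|---|---|
| GAPPS (2 sites) | 32 weeks | No |
| AMANHI (3 sites) | 32–36 weeks | No |
| GARBH-INi | 30–32 weeks | Only if delivery follows the visit |

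The GAPPS visit at 26–28 weeks touches the lower edge of the late window, hence the words clearly late. Stillbirths delivered before 32 weeks are in the same position. Table 2 gives 168 stillbirths at the five sites but does not split them by gestational age, so no size is computed for them.

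**3. Discrimination from absence alone.** For a yes/no flag,

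AUROC = 0.5 + [P(absent | case) − P(absent | non-case)]/2.

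For very preterm birth at the five sites, P(absent | case) = 1. Writing f for the share of other women without the late specimen, AUROC = 0.5 + (1 − f)/2 = 1 − f/2. The article gives no per-window counts, so f is an assumption.

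For all preterm birth, let s = 148/1587 = 0.093 be the share with structural absence, the remaining cases being absent at rate f. Then P(absent | case) = s + (1 − s)f, and AUROC = 0.5 + s(1 − f)/2.

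| f (assumed) | Very preterm birth | All preterm birth |
|---|---|---|
| 10% | 0.95 | 0.54 |
| 20% | 0.90 | 0.54 |
| 30% | 0.85 | 0.53 |
| 50% | 0.75 | 0.52 |

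The last column is a lower bound on the structural effect, because some births at 32–36 weeks also precede the late visit.

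**4. A rough anchor for f.** The article plans for "over 30 000 longitudinally collected maternal plasma samples". If three samples were intended for each of 16 221 women and losses were equal across windows, average absence would be 1 − 30 000/(3 × 16 221) = 1 − 30 000/48 663 = 38%, giving 1 − 0.383/2 = 0.81 for very preterm birth. Both conditions are assumptions.

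**5. Simulation.** With 16 221 women, 148 cases all lacking the late specimen, and markers that were pure noise, AUROC in held-out data was 1.00, 0.90 and 0.81 at f = 0, 20% and 38%. The results were the same whether the score was the absence flag or a model fitted after constant imputation.

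**The case against.** **Stage-specific models.** The strongest reply is that the plan already builds one model per outcome and stage, meant to describe risk at that point in pregnancy. Read naturally, a late-stage model covers women who are pregnant and sampled then, which would remove the problem. This stands in part: the design is compatible with a clean analysis. But the article does not state that restriction, the missing-data sentence favours keeping incomplete participants, and signatures across several time points are also an aim.

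**What is being imputed.** The sentence most naturally refers to absent assay layers, since nutrients, epigenomics and bioanalytes are measured only in subsets. A reader might infer that the plan will impute specimens dated after delivery, or that outcome leakage has been shown. The documents do not support either. They name XGBoost without saying that its own handling of missing values will be used. The flag and the constant imputation simulated above are illustrations, and imputing from earlier data without the outcome or a flag need not leak in this way. This makes the concern conditional, but does not rescue an unconditional assurance.

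**Every site, every case.** A reader might also infer that no very preterm birth anywhere has a late specimen and that the artefact would replicate at all six sites. Table 1 contradicts this: some of the 72 GARBH-INi cases can be sampled at 30–32 weeks, and an artefact learned elsewhere should transfer less well to that cohort. Even at the five sites the claim rests on scheduled weeks; actual sampling dates are not shown.

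**All preterm birth.** It is tempting to extend the large effect to preterm birth as a whole by supposing that, say, 30% of cases lack the specimen. No such share is in the documents. If 30% in total lacked it, the AUROC would be 0.5 + (0.30 − 0.10)/2 = 0.60 at f = 10%, and 0.50 at f = 30%.

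**Detail left elsewhere.** Full imputation rules may sit in an analysis plan not shown, and their absence here is no fault. The point concerns what the article asserts.

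**Conclusion.** The point holds in limited form. The unconditional no-bias statement cannot be supported for late-window or multi-time-point models that retain women without a late specimen. By the article's own schedule, all 148 very preterm births at the five GAPPS and AMANHI sites, and any stillbirth there before 32 weeks, lack that specimen because of the outcome. At GARBH-INi the same is true only of births before the visit.

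Under those conditions the potential distortion is large for very preterm birth and small for all preterm birth when only the very preterm share is counted. The sizes rest on the assumed absence rate in other women and on visits being held as scheduled. Early-window models are not exposed to this mechanism, and the stage-specific models escape it if limited to women undelivered and sampled at that stage.

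The supported conclusion is that the stated property fails and that the planned site validation would not reveal it among the five sites. It is not shown that the planned analysis leaks the outcome.

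**What to change.** 1. Delete the no-bias phrase, or qualify it by stating the missingness assumption and excluding specimens whose absence is caused by delivery or foetal death.
2. Define the at-risk set of each late or multi-time-point model as women still pregnant and sampled at that landmark, using only that specimen and earlier ones.
3. Treat any specimen due after delivery or foetal death as not applicable and never impute it. Limit imputation to features or layers of specimens that were collected.
4. Report, beside each such model, a model given only the missingness pattern, as a negative control. An omics model that does not beat it has shown nothing.

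The cost is analysis wording and one inexpensive extra model. The real loss is that late-window models for very preterm birth are dropped at the five GAPPS and AMANHI sites, where on schedule the data cannot exist; prediction of that outcome there then rests on early and mid-pregnancy specimens. Because analysis is under way, the change should be made before any late or multi-time-point model is interpreted.

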Comprehensive multi-cohort studies with harmonised clinical data and longitudinally collected biological specimens at time points standardised across sites and cohorts are required to address these challenges. The Multi-omics for Mothers and Infants (MOMI) Consortium was formed in response to this need. It brings together diverse pregnancy cohorts from low- and middle-income countries (LMICs) in Asia and Africa: the Alliance for Maternal and Newborn Health Improvement (AMANHI) from Pakistan, Bangladesh, Tanzania; the Global Alliance to Prevent Prematurity and Stillbirth (GAPPS) from Bangladesh and Zambia; and the Interdisciplinary Group for Advanced Research on Birth Outcomes – DBT India Initiative (GARBH-INi). This creates a unique resource of 24 321 pregnant women with well-phenotyped pregnancy outcomes and longitudinally collected biospecimens. The Consortium partnered with five analytics partners and three bioinformatics teams to analyse longitudinally collected specimens for genomics (Cincinnati Children’s Hospital, Ohio, USA), metabolomics (Sapient Bio, California, USA), proteomics (Max Planck Institute for Biochemistry, Martinsried, Germany), and nutrient testing (UC Davis, California, USA, and International Centre for Diarrhoeal Disease Research (icddr,b), Dhaka, Bangladesh). The vast dataset of the various multi-omics and nutrient analyses, in combination with the sociodemographic and clinical metadata, will enable the MOMI Consortium to identify causal pathways through data integration and validate predictive biomarkers to develop clinically relevant interventions for mitigating APOs.

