Due to the high cost-per-sample and medium/low sample throughput, a case-cohort study design categorised into the sub-cohort and nested case control study (**Figure 3**) was selected. The sub-cohort includes the longitudinal samples of approximately 30% of pregnant women in the full cohort and available cord blood samples for group I nutrient analysis (Figure S8 in the **Online Supplementary Document**). Nutrients of this group include vitamin A, D, E, folate, B12, total homocysteine, ferritin, transferrin receptor, iodine, minerals (copper, selenium, magnesium, calcium, phosphorus, iron, potassium, sodium), alpha-1-acid-glycoprotein, C-reactive protein, high-density lipoprotein, low-density lipoprotein, and triglycerides. It is noteworthy that the Group I Nutrient analyses will be performed by the icddr,b, representing the only in-country analysis. Group II nutrients (vitamins B1, B2, B3, B5, B6, B7, choline, and a targeted metabolomics panel) will be analysed in the longitudinal samples of PE, SB, and vPTB cases and their matched term controls (1:3 ratio). The B vitamins, choline and related metabolites will be measured by ultra-high performance liquid chromatography (UHPLC)- MS/MS and fatty acids and amino acids by UHPLC-MS/MS – MxP®Quant 500 XL kit [51,54].

As specimens of the GARBH-INi cohort will be analysed by the Translational Health Science and Technology Institute, India (THSTI), a harmonisation plan between THSTI and icddr,b, or between THSTI and UC Davis for nutrient group I or group II analyses, respectively, was developed. Institutions will apply standardised test methods, instrument calibration, quality control measures, external quality assurance schemes, and reporting methods. The joint analysis of the nutrient group I and II parameters from the GAPPS, AMANHI and GARBH-INi sites will allow for validation across sites and analytical platforms.

The placenta tissue analysis will be particularly valuable towards the goal of designing novel diagnostics or intervention strategies to prevent APOs, as several of the APOs are either entirely or partially attributable to placental dysfunction. These include early-onset PE, foetal growth restriction, and a subset of PTB cases. Since the placenta is in direct contact with maternal blood, placental APO signatures will likely be highly complementary to APO signatures in maternal blood and provide crucial information on the involvement of certain biological pathways.

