For non-machine learning association analyses, we will use a prespecified covariate framework grounded in clinical relevance and established epidemiologic confounders, including maternal age, body mass index, parity, GA at sampling, and study site. These variables will be incorporated within mixed-effects or hierarchical regression models to appropriately account for cohort structure and site-level heterogeneity, with model specifications defined *a prior* to avoid data-driven overfitting. To control for false-positive findings across the large number of molecular features tested, we will apply false discovery rate correction within each omics layer and, where appropriate, across integrated analyses.

Although statistical harmonisation approaches such as ComBat are effective at reducing batch effects, they may inadvertently remove meaningful biological or population-level differences between sites. Therefore, our primary framework prioritises external validation across sites as the most conservative test of reproducibility and transportability. Rather than relying solely on post hoc harmonisation, our primary strategy is to evaluate robustness and generalisability directly. Specifically, we will train models on subsets of study sites and validate them on held-out sites. This design allows us to assess real-world performance under true site-level variation, including differences in GA assessment, biospecimen handling, and sociodemographic context. This cross-site training and validation framework ensures that identified signatures are not artifacts of a single cohort, platform, or operational pipeline, but instead reflect patterns that are stable across diverse populations. Only models and associations that replicate across sites will be interpreted as biologically meaningful, providing a principled basis for pooled analyses. As a complementary, secondary analysis, we will apply ComBat-based correction and mixed-effects modelling to quantify and compare the impact of site-level harmonisation. This layered approach allows us to rigorously test whether pooled analyses are justified, distinguish technical from biological sources of heterogeneity, and preserve interpretability, while maintaining statistical rigor across structurally heterogeneous cohorts.

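### Holding out study sites cannot show that a proteomic or metabolomic signature is free of platform artefact, because the five AMANHI/GAPPS sites share one laboratory per assay

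*Protocol article*

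**What the plan says.** All references are to the protocol article.

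- **The safeguard.** Under Data Analysis and Data Integration, the primary strategy is to "train models on subsets of study sites and validate them on held-out sites". The site-level variation that this is meant to cover is described as "including differences in GA assessment, biospecimen handling, and sociodemographic context".
- **The property claimed for it.** The article states that this approach "ensures that identified signatures are not artifacts of a single cohort, platform, or operational pipeline, but instead reflect patterns that are stable across diverse populations".
- **The decision rule built on it.** "Only models and associations that replicate across sites will be interpreted as biologically meaningful, providing a principled basis for pooled analyses". The introductory text states the same criterion and extends it to clinical meaning.
- **Who runs the assays.** The introductory text lists the analytics partners, with one each for these layers: "metabolomics (Sapient Bio, California, USA), proteomics (Max Planck Institute for Biochemistry, Martinsried, Germany". Analytical Studies describes one plasma preparation workflow and one mass-spectrometer type for proteomics, and one metabolomics method. Data Analysis and Data Integration describes one computational pipeline.
- **GARBH-INi.** This sixth site is a planned validation cohort for MOMI findings (Study Design, Analytical Studies, and Data Analysis and Data Integration). The nutrient part of Analytical Studies begins a sentence with "As specimens of the GARBH-INi cohort will be analysed by the Translational Health Science and Technology Institute, India (THSTI" and goes on to a harmonisation plan with the two nutrient laboratories.

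**The concern.** A validation scheme tests only the factors that differ between the training data and the held-out data. Holding out Karachi or Pemba changes the population, the clinical procedures and the sample handling. It does not change the metabolomics or proteomics laboratory, the instrument, the sample preparation or the shared preprocessing. The article nevertheless credits the scheme with excluding single-platform artefacts, and it makes cross-site replication the criterion for biological meaning.

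At stake is what may be concluded from a replicated signature. The metabolomics method is expected to measure more than 11 000 features, of which more than 10 000 are unknown or novel. Shared-processing artefacts are harder to recognise among features without a known identity. A signature that replicates only among sites sharing an assay has been shown to transfer between populations on that assay, and no more.

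**Working it through.** The article gives no figure for this property, so there is none to reproduce. The check is a comparison of passages, followed by an illustration.

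**Step 1. What varies when an AMANHI or GAPPS site is held out**

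| Factor | Differs between training and held-out site? | Source |
|---|---|---|
| Population, sociodemographic context | Yes | Data Analysis and Data Integration |
| Gestational-age assessment, biospecimen handling | Yes | Data Analysis and Data Integration |
| Metabolomics laboratory and method | No, one partner | Introductory text; Analytical Studies |
| Proteomics laboratory, preparation, instrument type | No, one partner | Introductory text; Analytical Studies |
| Computational pipeline | No, one described | Data Analysis and Data Integration |

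The first two rows support the claim about a single cohort. They also support the claim about an operational pipeline if that means site operations. The last three rows do not support the claim about platform or shared processing.

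**Step 2. What an outcome-linked artefact would do**

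Inputs from Table 2 (PTB cases / pregnancies): Zambia 223/2576, GAPPS Bangladesh 384/3644, AMANHI Bangladesh 366/3000, Pakistan 372/2500, Tanzania 242/4501. These sum to 1587/16 221, which matches the combined column.

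Assumptions, none of them from the article:
- a feature with unit SD and no biological effect;
- an artefact that shifts cases by d SD equally at all five sites;
- all non-PTB pregnancies as comparators;
- passing means two-sided p<0.05 at every site.

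Per site, SE = √(1/n₁ + 1/n₀), and the probability of passing is Φ(d/SE − 1.96). For Zambia at d = 0.2, n₀ = 2576 − 223 = 2353, SE = √(1/223 + 1/2353) = 0.0701, d/SE = 2.85, and the probability is Φ(0.89) = 0.81.

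| d | Zambia | GAPPS Bangladesh | AMANHI Bangladesh | Pakistan | Tanzania | Product (all five) |
|---|---|---|---|---|---|---|
| 0.2 | 0.81 | 0.96 | 0.95 | 0.95 | 0.86 | 0.60 |
| 0.3 | 0.99 | >0.99 | >0.99 | >0.99 | >0.99 | 0.98 |

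**Step 3. Leave-one-site-out simulation (200 replicates, same counts)**

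Passing here means a held-out AUC above 0.5 at z>1.96 at all five sites. The sixth cohort has GARBH-INi's size (764/8100).

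| Shift at the five sites | Shift in sixth cohort | Mean AUC at held-out sites | Passes all five | AUC in sixth cohort |
|---|---|---|---|---|
| 0 | 0 | 0.50 | 0% | 0.50 |
| 0.2 | 0 | 0.56 | 60% | 0.50 |
| 0.3 | 0 | 0.58 | 98% | 0.50 |
| 0.5 | 0 | 0.64 | 100% | 0.50 |
| 0.5 | 0.5 | 0.64 | 100% | 0.64 |

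The first row shows that a feature with no link to outcome does not pass. The next three rows show that a cohort assayed without the artefact exposes it. The last row shows that a sixth cohort sharing the artefact does not.

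The pass rates are ordinary power for the assumed shift, so they say nothing about how likely such an artefact is. What does not depend on the assumptions is that, within a shared platform, the rule cannot separate an artefact from a true effect of the same size.

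**The case against.** The case on the other side is substantial, and much of it stands.

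- **GARBH-INi is part of the design.** It is one of six sites, its use as a validation cohort is already planned, and the nutrient text expressly foresees validation across analytical platforms. A reader might infer that a platform artefact passes at every site of the Consortium. The article does not support that. An artefact tied to one laboratory could fail in GARBH-INi if its specimens are measured elsewhere. But the replication rule does not make that confirmation a condition, and the second laboratory is named only in the nutrient section. Leaving the proteomic and metabolomic laboratory unnamed is no fault in a condensed article. It only means that GARBH-INi cannot yet be relied on to support the platform claim.
- **The operational pipeline may mean site operations.** The surrounding text on biospecimen handling makes that reading natural, and holding out a site does test it. It would be wrong to infer that the scheme tests nothing beyond the cohort. The word platform has no such alternative reading.
- **Most artefacts would not pass.** They must follow case status in the same direction within sites. Nothing in the article suggests that cases and comparators are assayed separately. Metabolomics and proteomics are planned for all longitudinal maternal specimens.
- **Other safeguards exist.** Reference samples, pooled replicates in each preparation batch, metabolomic quality control, and modelling of batch and site effects all reduce the risk. Structural identification is also described before metabolomic validation. A reader might infer that artefacts will be reported as biology; the article does not support so definite a prediction. These measures lower the chance of a shared artefact, but none of them is the held-out-site test to which the sentence attributes the protection.

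**Conclusion.** The concern holds in a limited form. For proteomics and metabolomics at the five AMANHI and GAPPS sites, held-out-site validation does not have the platform property claimed for it, because the platform is constant across those sites. This rests on the article's own assignment of one laboratory per assay and on the site being the only unit held out. The claim stands for cohort- and site-level artefacts, including site operations.

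The size of the risk cannot be given from the article. The 60% and 98% figures illustrate how readily an outcome-linked artefact of 0.2 or 0.3 SD would pass, under shift sizes and a pass rule that are assumptions. Whether GARBH-INi closes the gap depends on where, and on what platform, its proteomic and metabolomic validation data are produced. The Data Harmonisation section also says that GARBH-INi analysis pipelines have been harmonised with the Consortium's, so an artefact of shared computation might persist even with a different laboratory. The point should be corrected because the rule for biological meaning rests on the sentence.

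**What to change.** 1. Limit the sentence under Data Analysis and Data Integration to artefacts of a single cohort or of site-level operations, and remove platform from what held-out-site validation is said to ensure.
2. Call a proteomic or metabolomic signature platform-independent only if it is confirmed in the GARBH-INi validation already planned, using a different laboratory or an orthogonal or targeted assay. State the laboratory and platform for each of these layers.
3. Report a signature that replicates only among the five AMANHI and GAPPS sites as replicated across sites on a shared platform.
4. If GARBH-INi proteomics or metabolomics uses the same platform, drop the platform claim for that layer, and name within-laboratory quality control and batch modelling as the safeguard relied on.

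The cost is a change of wording and a reporting label. No new specimens are needed if the planned validation already uses another laboratory or assay. The downside is that fewer signatures will carry the full claim.
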